Time to Meaningful Analgesia	Defined as a 44% change in NRS pain score from initial pain score. The time will be taken as time of meaningful analgesia minus time of first administration	If 44% change not achieved, we will score this as meaningful analgesia not achieved
Time to Peak Analgesia	Measured as the time when lowest NRS pain score, relative to initial pain score, is achieved minus time of first administration	
Duration of Analgesia	Measured as the time period in which patient pain scores have consecutively decreased or remained stationary (There may be different instances of this per patient)	
Requirement for Rescue Analgesia	We will record whether a patient has needed rescue analgesia and which analgesia was administered, Entonox, paracetamol, ibuprofen, or other	
Proportion of patients with pain intensity score below 4/10 on NRS scale	At hospital arrival the research paramedic will record a NRS pain score. We will provide the proportion, as a percentage, of each patient that achieved a score < 4/10	If there is no hospital arrival score, we will use the scores recorded in the ambulance journey
Vital Signs	At each observation time, the respiratory rate (bpm), oxygen saturations (%), heart rate (bpm), blood pressure (mmHg) and their Glasgow Coma Scale (GCS)	
Glasgow Coma Scale	Three subscales measuring eyes, verbal, and motor response of each patient. The scales are as such: Eyes 1–4 Verbal 1–5 Motor 1–6	
Global Impression of Change	Using a 7-point Likert scale. The options offered ranging from ‘very much improved’ to ‘very much worse’	
Side effects and adverse events	Measured in the following categories, ‘Airway’, ‘Respiratory’, ‘Cardiovascular’, ‘Neurologic’, and ‘other’	
Ambulance job cycle time	Time taken from arrival on scene to hospital arrival	
Number of ambulance resources	Number of doctors, paramedics, doctors, and vehicles attending scene	
Cumulative IMP doses administered	Total dose of IMP administered	
CT scan use	If patient had a CT scan and how many	
Hospital or ICU admission	Yes; no option if patient is admitted to hospital or ICU	
Length of stay in ED, ICU, or hospital	Classed as date and time of admission to date and time of discharge	
BPI-SF at 3 and 6 Months		

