### Data analysis

The statistical analysis will follow the estimand framework [46]. Primary analysis will be by intention to treat. The primary outcome will be the SPID, a measure of the area under the curve of the pain score difference from baseline over time. The primary outcome will be analysed using a linear regression. Both unadjusted and adjusted (for important covariates) estimates and 95% confidence intervals for the treatment effect will be obtained. The adjusted estimates will form the basis for the primary analysis. Descriptive summaries of the outcomes will be presented as frequencies or means and medians. For the adjusted estimates, the covariates used will be age (< 60; ≥ 60 years), gender, weight and alternative parenteral IV paracetamol prior to randomisation (as a dichotomy split by yes or no). Age and gender have been chosen as covariates as these groups can experience pain differently, administration of IV paracetamol prior to randomisation is included as a covariate as it is an adjunctive treatment that may impact pain response. Weight is included as a covariate since different weight groups have different requirement for an adequate dose of IMP. For continuous secondary outcomes, analysis will be carried out in a similar way to the primary outcome. For categorical outcomes, logistic regression models will be used. Participant vital signs are recorded in a longitudinal format, for these outcomes we will use a mixed effect model.

Various intercurrent events have been identified for this trial, in line with the estimand framework [46], and approaches to dealing with these have been considered. For discontinuation of the allocated treatment and use of rescue analgesia, we will follow the treatment policy, where the data is analysed as observed. Compliance with administration of the trial drug as per the trial protocol will be monitored. If there is a noticeable degree of non-compliance, we will carry out a complier average casual effects (CACE) analysis [47, 48]. If sufficient data permits, sensitivity analysis will be conducted on a modified intention to treat population, excluding participants that were randomised but the drug was not given. Again, if sufficient data permits, participant deaths will be analysed using Pocock’s win ratio method, this allows death to be interpreted as a participant outcome and infer if the intervention is significantly better than the standard care having considered the clinical priority.

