Item missingness is expected for the primary outcome due to the method of recording data used in the trial, however the primary outcome is a measure of the area under a curve, therefore if two pain measurements are recorded the primary outcome can still be measured. Imputation methods have been considered for missingness, but methods such as last observation carried forward are not reliable due to the variability of pain scores, and we cannot assume that pain scores are missing at random therefore multiple imputation is also not feasible. Analyses and template tables will be reported in a detailed statistical analysis plan for review and approval by the Data Monitoring Committee (DMC), prior to final statistical analysis of the data.

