### Health economic evaluation

A health economic evaluation has been embedded into the PACKMaN trial. The economic evaluation will take the form of a within-trial cost-effectiveness analysis, conducted from the perspective of the UK NHS and personal social services [49]. Estimates of economic costs will capture resource use associated with the pre-hospital emergency response and broader utilisation of hospital and community-based health and social care services. Resource use in the pre-hospital stage will be extracted from trial case report forms completed by research paramedics. This will include the number of paramedic staff, technicians, doctors, and ambulance staff attending the patient, in addition to transport vehicle, duration of emergency response and cumulative morphine or ketamine doses administered, and medication for treatment of adverse events. Additionally, index admission hospitalisation data resource use will be extracted, this includes length of stay, and number of days receiving critical care and associated critical care level. Resource use questions completed by participants at each assessment point during the study follow-up will provide a profile of all other hospital inpatient and outpatient services, community health and social care encounters, prescribed medications, NHS supplies, time off work and out of pocket medical expenses. Health-related quality of life will be measured using the EQ-5D-5L at three and six months after randomisation. For ethical, logistical, and pragmatic reasons, it is not possible to capture baseline EQ-5D-5L measurements in patients suffering acute pain following trauma within this trial. This is not uncommon within trials in emergency and critical care settings [50]. The baseline analysis for the health economic evaluation will use a fixed baseline approach for EQ-5D-5L health utilities for all participants. This fixed value will be derived by mapping the ‘typical’ acute pain trauma case to the EQ-5D-5L using expert opinion. The sensitivity of this assumption will be tested within sensitivity analyses. Sensitivity analyses will include assigning different values to patients according to severity as determined by registration to the Trauma Audit and Research Network (TARN). TARN can be used as a proxy for severity as the most serious trauma patients will be registered onto TARN whilst less severe cases will not (non-TARN). We will then use expert opinion to estimate a baseline EQ-5D profile for both TARN and non-TARN patients. We will estimate QALY profiles for each participant over a six-month time horizon using the baseline-adjusted area-under-the curve method. We will fit a bivariate regression of costs and QALYs, with multiple imputation of missing data. We will estimate the incremental cost per QALY gained for the comparator interventions from incremental costs and incremental QALYs generated from the regressions. Cost-effectiveness estimates will also be generated for subgroups as specified in the health economics analysis plan.

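### Doubt about missing at random does not make multiple imputation infeasible, and the two-score rule leaves SPID dependent on when pain scores were written down

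*Protocol article*

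**What the plan says.** The Data analysis section acknowledges the problem: "Item missingness is expected for the primary outcome due to the method of recording data used in the trial". It then rejects two remedies. On carrying scores forward, it says "methods such as last observation carried forward are not reliable due to the variability of pain scores". On imputation, it says "we cannot assume that pain scores are missing at random therefore multiple imputation is also not feasible". What remains is the statement that, because SPID is an area under a curve, "if two pain measurements are recorded the primary outcome can still be measured". Neither the timing of those two scores nor the presence of an arrival score is required. The same section states "Primary analysis will be by intention to treat".

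Two other places decide what this means in practice:

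- Outcomes, Table 3 defines SPID as the sum over recorded scores of (T_i − T_{i−1}) × PID_i, with time in hours and no division by duration.
- The Primary outcome section sets the window from randomisation to hospital arrival, fixes no scoring interval, and asks only that scores be documented regularly.

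For the proportion below 4/10 at arrival, Table 3 adds: "If there is no hospital arrival score, we will use the scores recorded in the ambulance journey".

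**The concern.** The reasoning runs the wrong way. If scores may be missing for reasons tied to the pain itself, computing SPID from whatever was recorded does not avoid an assumption about the missing ones. It makes one silently, through the formula. Multiple imputation, by contrast, lets the assumption be stated and varied.

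The silent assumption has three parts. Each gap between scores takes the value of the score that closes it. The stretch from the last score to arrival contributes nothing, which has the same effect as scoring no relief there. A randomised patient with no score after baseline has no SPID and drops out.

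Scoring may plausibly thin out or stop because the patient is comfortable, drowsy, distressed or close to hospital. If such reasons operate differently under ketamine and morphine, the primary contrast is biased.

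**Working it through.** **The plan's own figures.** The article gives no figure for score missingness, journey time or scoring frequency. The nearest figure is the sample size, which reproduces: 2 × 3.0² × (1.960 + 1.282)² / 1² = 189.1 per arm; 189.1 / 0.85 = 222.5, so 223 per arm and 446 in total. It is not at issue here.

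**Illustration 1: falling pain (assumed).** PID(t) = 5(1 − exp(−t/10)), t in minutes, 40-minute journey. PID at 10, 20, 30 and 40 min is 3.161, 4.323, 4.751 and 4.908. The true area is 5 × [40 − 10(1 − e⁻⁴)] / 60 = 2.515 point-hours.

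The Table 3 sum with scores every 10 minutes is (10/60) × (3.161 + 4.323 + 4.751 + 4.908) = 2.86. The other rows follow in the same way; the trapezoid averages the two end scores of each interval.

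| Scores after baseline | Table 3 sum | Error | Trapezoid | Error |
|---|---|---|---|---|
| Arrival only | 3.27 | +30% | 1.64 | −35% |
| Every 20 min | 3.08 | +22% | 2.26 | −10% |
| Every 10 min | 2.86 | +14% | 2.45 | −3% |
| Every 5 min | 2.70 | +7% | 2.50 | −1% |

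**Scoring stops at 20 of 40 minutes (same curve).**

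- One score at 20 min: (20/60) × 4.323 = 1.44, which is 57% of 2.515.
- Scores every 5 min to 20 min: 1.11, which is 44%.
- Exact area to 20 min, for comparison: 0.946, which is 38%.

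**Illustration 2: rebound (assumed).** NRS falls linearly from 9 to 4 by 20 min, stays there to 40 min, then rises to 7 at 60 min. The true area is (20 × 5/2 + 20 × 5 + 20 × (5 + 2)/2) / 60 = 220/60 = 3.67.

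- Scores at 0 and 60 min only: 1 × 2 = 2.00, an error of −45%.
- Every 20 min: (20/60) × (5 + 5 + 2) = 4.00, an error of +9%.

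The sign of the gap error therefore depends on the course of pain.

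**What an imputed arrival score does (curve 1, scores at 0, 10 and 20 min).**

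- Table 3 sum as it stands: (10/60) × (3.161 + 4.323) = 1.25, about 50% of the true area.
- Trapezoid to 20 min: (10/60) × (3.161/2 + (3.161 + 4.323)/2) = 0.887.
- If the arrival score is imputed at its true 4.908, the tail adds (20/60) × (4.323 + 4.908)/2 = 1.539. The total is 2.43, an error of about −4%.

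**What dividing by observed time does.** Truncated at 20 min, the mean PID is 0.946 / (20/60) = 2.84. The full-window mean is 2.515 / (40/60) = 3.77. The shortfall is 25%, so the truncation bias remains.

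**The case against.** The case on the other side is substantial and limits the point in several ways.

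- **All unrecorded time counts as no relief.** A reader might infer this, but Table 3 does not support it. Only the tail after the last score adds zero. Gaps take the next PID, and sparse scoring inflates SPID only while pain is falling.
- **The tail is common.** Table 3 plans an arrival score and the Primary outcome section asks for regular scoring up to arrival, so the tail opens only where the arrival score is missing. No rate is given. The 15% in the Sample size section is an assumed withdrawal/non-response rate, not a rate of missing scores within the journey.
- **Many patients drop out of the intention-to-treat analysis.** Eligibility requires a reported score of at least 7/10, so every eligible patient has a baseline score. Only those with nothing after baseline are lost.
- **The plan contradicts itself on imputation.** The Health economic evaluation section says "We will fit a bivariate regression of costs and QALYs, with multiple imputation of missing data". Those are different variables, partly from posted questionnaires, and a different missingness assumption is legitimate. The ambulance-score substitute for the below-4/10 outcome sits awkwardly with the rejection of last observation carried forward. However, it concerns a secondary outcome and does not say which ambulance score is used.
- **No sensitivity analysis is planned.** This cannot be known. The article defers detail to a statistical analysis plan that is not shown.
- **Blinding protects the comparison.** It makes recording habits less likely to differ by arm, but it cannot rule out differences caused by the drugs' own effects on patients.

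None of this rescues the stated inference or the two-score rule, both of which the article fixes in so many words.

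**Conclusion.** The point holds in limited form. The stated reason for excluding multiple imputation does not follow, and the rule put in its place makes the primary outcome depend on when scores were recorded.

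On the assumed falling curve, the error in one patient's SPID is +7% to +30% by scoring frequency alone. SPID is 44–57% of the true area if scoring stops halfway. After a rebound the error can be negative.

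These percentages must not be read as bias in the treatment effect. They are errors in an individual's value on assumed curves and journey times. Bias between arms arises only if recording, or its relation to pain, differs by arm, and the article gives nothing from which to size that. The direction of each mechanism follows from the Table 3 formula; its amount does not.

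The matter is worth correcting because the authors themselves decline to assume missing at random.

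**What to change.** 1. Delete the statement that multiple imputation is not feasible.
2. Compute SPID by the trapezoidal rule over the whole window from randomisation to hospital arrival. Arrival time is already needed for ambulance job cycle time, so the end of the window should be known when the score is not.
3. Where the arrival score is missing, or there is no post-baseline score, multiply impute the arrival score by arm from baseline NRS, earlier scores, rescue use, dose given and vital signs, so that all randomised patients are included.
4. Add delta-adjusted (tipping-point) imputation by arm to show how far departures from missing at random must go to change the conclusion.
5. Keep the available-score SPID as a sensitivity analysis.
6. Use the same imputation for the below-4/10 outcome at arrival, with the ambulance-score substitute as a sensitivity analysis.
7. Report a time-averaged PID (area divided by observed time), if at all, only as a declared supplementary measure. It is a different estimand and does not remove truncation bias.

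The trapezoid has a limit that should be stated: with only a baseline and an arrival score it errs by −35% on the curve above, no better than the present rule. Because scoring times are free, the arrival score is the one clearly defined missing item. Imputing scores within the journey would first need an imposed time grid.

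The cost is wording in the analysis plan, some extra programming and more sensitivity results to report. No new data are needed. The article describes recruitment as ongoing and the analysis plan as still to be approved before final analysis.

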#### Subgroup analysis

We have selected the following subgroups to explore interactions relating to age, gender and the administration of intravenous paracetamol prior to randomisation. The primary outcome will be used as the dependent variable, interaction between the subgroup variable and treatment will be included as an independent variable. Linear regression models will be used to assess the subgroup effect, using interaction terms, subgroup by treatment, to measure the effect of each subgroup.

#### Data security

Participant data are being stored on a secure database in accordance with the Data Protection Act (1998). A unique trial identification number is used on all follow-up questionnaires. Warwick clinical trials unit does not receive nor process any personal identifiable data for this trial.

### Data collection and management

Source documents are where data are first recorded, and from which participants’ case report form (CRF) data are obtained. These include, but are not limited to, ambulance service records and hospital records (from which secondary outcome data will be collected from)*.* Patient eligibility and ambulance data will be collected from electronic patient records, whereas patient hospital data will be obtained from retrospectively from medical records. Follow up data is obtained from questionnaire packs posted out to participants that have consented to receive them.

On all trial-specific documents, other than the signed consent form, the participant will be referred to by the trial participant number/code, not by name. Data will be entered on to the trial database by the research team.

### Health economic evaluation

A health economic evaluation has been embedded into the PACKMaN trial. The economic evaluation will take the form of a within-trial cost-effectiveness analysis, conducted from the perspective of the UK NHS and personal social services [49]. Estimates of economic costs will capture resource use associated with the pre-hospital emergency response and broader utilisation of hospital and community-based health and social care services. Resource use in the pre-hospital stage will be extracted from trial case report forms completed by research paramedics. This will include the number of paramedic staff, technicians, doctors, and ambulance staff attending the patient, in addition to transport vehicle, duration of emergency response and cumulative morphine or ketamine doses administered, and medication for treatment of adverse events. Additionally, index admission hospitalisation data resource use will be extracted, this includes length of stay, and number of days receiving critical care and associated critical care level. Resource use questions completed by participants at each assessment point during the study follow-up will provide a profile of all other hospital inpatient and outpatient services, community health and social care encounters, prescribed medications, NHS supplies, time off work and out of pocket medical expenses. Health-related quality of life will be measured using the EQ-5D-5L at three and six months after randomisation. For ethical, logistical, and pragmatic reasons, it is not possible to capture baseline EQ-5D-5L measurements in patients suffering acute pain following trauma within this trial. This is not uncommon within trials in emergency and critical care settings [50]. The baseline analysis for the health economic evaluation will use a fixed baseline approach for EQ-5D-5L health utilities for all participants. This fixed value will be derived by mapping the ‘typical’ acute pain trauma case to the EQ-5D-5L using expert opinion. The sensitivity of this assumption will be tested within sensitivity analyses. Sensitivity analyses will include assigning different values to patients according to severity as determined by registration to the Trauma Audit and Research Network (TARN). TARN can be used as a proxy for severity as the most serious trauma patients will be registered onto TARN whilst less severe cases will not (non-TARN). We will then use expert opinion to estimate a baseline EQ-5D profile for both TARN and non-TARN patients. We will estimate QALY profiles for each participant over a six-month time horizon using the baseline-adjusted area-under-the curve method. We will fit a bivariate regression of costs and QALYs, with multiple imputation of missing data. We will estimate the incremental cost per QALY gained for the comparator interventions from incremental costs and incremental QALYs generated from the regressions. Cost-effectiveness estimates will also be generated for subgroups as specified in the health economics analysis plan.

The primary trial-based analysis will focus on the costs and QALYs accrued during the trial period. There is however potential for costs and benefits to accrue beyond the trial period. If outcomes have not converged by the 6 month timepoint we will consider extrapolating the results over a longer time horizon using a decision analytic model. This would involve combining the trial data with external sources to estimate the long-term cost-effectiveness of the intervention. Any costs and benefits accruing after the first year would be discounted at a rate of 3.5% per year and full probabilistic sensitivity analysis would be conducted in line with the NICE reference case [49]. A decision around the construction of a separate decision analytic model will be made following discussion between the health economists and the trial team following preliminary analysis of the data. This will be informed by considerations such as the conclusiveness and direction of within trial results. For example, if the control dominates the intervention and extrapolation would only increase the strength of this result then there is little need to extrapolate further as the intervention should be rejected. The decision to extrapolate cost-effectiveness will also take into account the availability and quality of external data to inform model parameter inputs.

### Adverse events

The trial is enrolling patients with acute traumatic injuries which may be immediately life threatening, or result in hospitalisation, persistent or significant disability/incapacity and or death. Potential adverse events are captured on the case report form and investigated by the research paramedic in the first instance. The research paramedic passes the results of their investigation to the PI to determine if the event is an adverse event or not. The trial team are then informed of the outcome as required. In addition, hospital clinicians are able to report clinical concerns to the research paramedic for review that will similarly be reported via the PI to the CI and onward as necessary.

Clinically predictable side effects will be captured but may not be classified as adverse events. For example, morphine is known to cause respiratory depression. A reduction in respiratory rate will be captured on case report forms. If no intervention is required, this will not be classified as an adverse event. However, if the treating paramedic has to assist ventilations of administer naloxone, then this would be classified as an adverse event.

The following adverse events are captured on the case report form as secondary outcomes. If deemed serious they will also be recorded and reported using the SAE form.Airway: vomiting, aspiration, advanced airway managementRespiratory: desaturation, need for ventilatory supportCardiovascular: arrhythmia, hypotension and hypertensionNeurologic: sedation, excitatory movements, adverse behavioural reactionsOther: nausea, allergic reaction

Serious adverse events which are not related to the acute traumatic injury, or are complications resulting from the IMP administration to 30 days post trial drug will be reported to the PACKMaN Trial team as soon as possible and within 24 h of the research staff becoming aware of the event.

